### Data Management

Data management in this clinical study adhered to stringent guidelines to ensure the accuracy, reliability, and integrity of the collected information. Upon the participants’ assessments, the research team promptly entered the data into CRFs and electronic CRFs. Source documents and CRFs were securely stored in restricted-access areas, limited solely to the study team. Electronic CRFs were password-protected and stored in secure, access-restricted computer systems.

Data entered by the study personnel was subjected to meticulous cross-verification by the principal investigators at the study site, ensuring the reliability of the data. Rigorous quality measures were implemented, such as regular audits, to identify and address any discrepancies in the data. The data management practices adhered to regulatory guidelines and ethical principles, prioritizing the protection of participants’ rights.

### Statistical Methods

The categorical data will be presented as numbers (percentages) and compared between groups using the *χ*^2^ test, while within-group comparisons will be performed by using the McNemar or Cochran Q-test. Continuous data following a normal distribution will be reported as mean (SD), and between-group comparisons will be performed using an independent sample *t*-test. Within-group comparisons for normal data will be performed using a paired sample *t*-test/repeated measures ANOVA. Nonnormal data will be reported as median (first quartile, third quartile), and between-group comparisons will be conducted using the Mann-Whitney test. Within-group comparison will be done using the Wilcoxon signed-rank test or Friedman test. Baseline variables, such as age, prior altitude exposure, and hydration-related indicators, will be examined descriptively and adjusted in multivariable models where relevant. Regression analysis will be performed to study the effect of confounding variables on the incidence of AMS. The data of participants having early descent will be analyzed with censored data models. A *P* value less than .05 will be considered significant. The SPSS version 28.0 is being used for statistical analysis.

The modified intention-to-treat analysis approach will be applied to handle missing data. The missing data for all participants for whom data are available for at least one visit post-baseline will be imputed. The last observation carried forward method will be used for imputing the missing values.

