## Introduction

### Background

High-altitude illness (HAI) is the collective term used for various debilitating health conditions that can affect individuals who are not acclimatized and ascend rapidly to high altitudes within 6 to 12 hours of their ascent to high altitude [1,2]. Conventionally, 2500 meters has been used as the threshold for HAI [2]. The spectrum of HAI encompasses various conditions that can range from mild to severe, among which the most typical are acute mountain sickness (AMS), high-altitude cerebral edema, and high-altitude pulmonary edema (HAPE). High-altitude cerebral edema and HAPE occur much less frequently than AMS but are potentially fatal. The risk factors for HAI are the rate of ascent, high altitude reached (especially the sleeping altitude), previous high-altitude exposure, and individual susceptibility [1,3,4]. AMS is a common clinical presentation in individuals venturing over 2500 meters and above [5]. The prevalence and severity of AMS rise with increasing altitude. It occurs in approximately 10% to 25% of nonacclimatized individuals at 2500 meters, which may increase to 50% to 85% at an altitude of 4500 to 5500 meters [2,6-8]. The pathophysiology of AMS includes relative hypoventilation, impaired gas exchange, increased sympathetic activity, fluid retention and redistribution, and raised intracranial pressure in case of moderate to severe AMS [1,5]. AMS presents with a group of nonspecific symptoms such as headache (primary defining symptom), gastrointestinal symptoms (anorexia, nausea, or vomiting), fatigue and/or weakness, dizziness, or disturbed sleep [9].

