### Sample Size

Based on the findings from a previous study on similar conditions, the anticipated incidence of AMS within the CG was 25%, while the assumed incidence in the AG was 18% [7]. To achieve a statistical power of 90% and a CI of 95%, an initial sample size of 722 per group was calculated. Accounting for an expected attrition rate of 15%, the final sample size for each group was determined to be 830 participants (N=1660 in total). The sample size of 1660 participants was stratified into stage I high altitude and stage II high altitude. A total of 830 participants were included from stage II high altitude, while the remaining 830 were from stage I high altitude. The participants studied at each of the 2 altitude stages were randomly allocated to the AG and CG.

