### Randomization

Block randomization with unequal block sizes randomly assigned participants to either the AG or CG with a 1:1 allocation to minimize predictability. Block randomization was implemented separately for stage I and stage II participants to ensure balanced allocation within each altitude-exposure setting. The SPSS version 28.0 (IBM) was used to generate the random number sequences. An independent statistician not involved in the participants’ enrollment and assessment generated the randomization sequence.

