### Allocation Concealment

Sequentially numbered, opaque, sealed envelopes were used to ensure allocation concealment. The participant’s enrollment number was printed at the top of the envelope, and a slip indicating the participant’s allocated group was kept inside. After completing all baseline assessments, the research staff provided the sealed envelope to the eligible participant. The participant opened the envelope and was then assigned to the group as indicated on the slip inside. The opened envelope and the printed slip were attached to the participant’s CRF for record and trial monitoring.

Participants assigned to the 2 study groups were housed in separate barracks throughout the study to prevent any protocol violations and minimize the risk of contamination bias. Further, yoga sessions and supplement distribution were conducted at designated areas accessible only to the intervention group, with attendance monitored by site instructors. The CG did not receive access to these sessions or materials, reducing the likelihood of unintentional participation. Study staff members were instructed to avoid sharing intervention-related information with control-group participants.

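### Randomization is stratified by altitude stage, but the only between-group test named for AMS incidence is an unstratified chi-square test, and stage is not a named adjustment variable

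*Protocol article*

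**What the plan says.** All references are to the protocol article.

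- **Randomization:** "Block randomization was implemented separately for stage I and stage II participants to ensure balanced allocation within each" altitude setting. Sample Size puts 830 participants in each stage, allocated 1:1.
- **Background:** "The prevalence and severity of AMS rise with increasing altitude". It gives 10% to 25% at 2500 m and 50% to 85% at 4500 to 5500 m in people who are not acclimatized. Strengths and Limitations accepts that stage may affect how symptoms begin.
- **Statistical Methods, test:** "The categorical data will be presented as numbers (percentages) and compared between groups using the" chi-square test. No stratified version is named.
- **Statistical Methods, adjustment:** baseline variables, with age, prior altitude exposure and hydration indicators as examples, will be "adjusted in multivariable models where relevant". A regression for confounders of AMS incidence is also planned. Stage is not named in either place, and the rank of the regression relative to the chi-square test is not given.
- **Sample Size:** one pair of rates serves both stages: "the anticipated incidence of AMS within the CG was 25%, while the assumed incidence in the AG was 18"%. Then: "To achieve a statistical power of 90% and a CI of 95%, an initial sample size of 722 per group was calculated".
- **Allocation Concealment:** the two arms were "housed in separate barracks throughout the study to prevent any protocol violations". The number and size of barracks are not given.

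**The concern.** When randomization is restricted within strata, between-stratum variation is removed from the treatment comparison by design. An analysis that ignores the strata leaves that variation in the standard error. If stage predicts AMS, the unstratified test rejects too rarely under the null and loses some power.

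A second issue is discretion. An unadjusted test and a regression are both planned for the same endpoint, with no stated order. Adjustment depends on relevance, and the variables listed are only examples. In an open-label trial with a symptom-score endpoint, it should be settled beforehand which result answers the primary question.

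Segregated housing raises a separate question. Participants in one barrack may have correlated outcomes, which would push the error in the opposite direction.

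**Working it through.** **1. The plan's own figure.** Inputs from Sample Size: 25% vs 18%, 90% power, 95% confidence read as two-sided alpha 0.05. With pooled variance and no continuity correction, p̄ = 0.215:

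n = [1.960·√(2·0.215·0.785) + 1.282·√(0.1875 + 0.1476)]² / 0.07² = (1.139 + 0.742)² / 0.0049 ≈ 722 per group.

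This matches. The design calculation is therefore an unstratified test on independent observations, with no stage-specific rates and no design effect.

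**2. Evaluable number.** 830 × 0.85 = 705.5, taken as 706 per arm (353 per arm per stage). Power of the plain test at 706 is 89.4%, which is the baseline below.

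**3. Effect of ignoring stage.** The article gives no stage-specific rates, so the stage I/II control rates c₁/c₂ are assumptions. Stages are of equal size, with a common odds ratio from 25% vs 18%: (0.18/0.82)/(0.25/0.75) = 0.659.

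- SE ratio, unstratified to stratified, under the planned effect: √[p̄(1−p̄) / mean of p̄ₛ(1−p̄ₛ)], where p̄ₛ averages the two arms within stage s.
- True alpha of the plain test: 2·[1 − Φ(1.960·√(C(1−C) / mean of cₛ(1−cₛ)))], where C is the mean of c₁ and c₂.

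Worked at 20/30%: Ayush rates are 14.1% and 22.0%. The SE ratio is √(0.1690/0.1670) = 1.006. The alpha ratio is √(0.1875/0.185) = 1.0067, so alpha = 0.0485.

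Worked at 10/50%: Ayush rates are 6.8% and 39.7%. The SE ratio is √(0.1954/0.1622) = 1.098. The alpha ratio is √(0.21/0.17) = 1.111, so alpha = 0.0294.

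| Assumed control rates, stage I/II | SE too large by | True alpha (formula) | Power, plain | Power, stratified |
|---|---|---|---|---|
| 25/25% | 0% | 0.050 | 89.4% | 89.4% |
| 20/30% | 0.6% | 0.0485 | 88.8% | 89.1% |
| 15/35% | 2.4% | 0.044 | 87.1% | 88.1% |
| 10/40% | 5.7% | 0.037 | 83.6% | 86.3% |
| 10/50% | 9.8% | 0.029 | 84.1% | 88.3% |

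Simulation with 415 per arm per stage and 200,000 runs gave alpha of 0.0483, 0.0355 and 0.0300 for the plain test at 20/30%, 10/40% and 10/50%. The Cochran-Mantel-Haenszel test gave 0.0497, 0.0486 and 0.0504.

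**4. Which row applies depends on the AMS window.** The Abstract counts the first 7 days from baseline, and Outcome Measures places those 7 days at stage I altitude. If only those days count, both strata are scored at the same altitude and the first row is the closest. If the 4 further days at stage II altitude also count, stage II participants have higher exposure and more days at risk, and a lower row becomes plausible.

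**5. Barracks, for illustration only.** Design effect = 1 + (m − 1)·ICC. Neither barrack size m nor the ICC is in the article, so both are assumed.

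- m = 20, ICC 0.001: 1 + 19·0.001 = 1.02; alpha 0.052; power 88.8%.
- m = 20, ICC 0.01: 1 + 19·0.01 = 1.19; alpha 0.072; power 83.6%.
- m = 40, ICC 0.02: 1 + 39·0.02 = 1.78; alpha 0.142; power 67.0%.

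Power uses 706 divided by the design effect.

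**The case against.** The strongest reply has four parts.

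- **Adjustment is already planned.** Statistical Methods names prior altitude exposure and a regression on AMS incidence, and model details are commonly left to an analysis plan that is not shown here. This stands against any claim that prognostic data are wasted. It does not explain why the randomization stratum is absent from the named variables or which analysis is primary.
- **Chi-square is stated for categorical data in general.** That it is the primary test is a fair inference, because AMS is reported as a proportion, but the article does not say so.
- **Wide stage splits are poorly supported.** Stage II ends at 15,000 ft (about 4572 m), so it barely reaches the 4500 to 5500 m band in the Background, and stage II participants acclimatize at stage I first. The 10/50% split also averages 30%, against the planned 25%. A split of 25/85% would make the SE 25.6% too large, but it averages 55% and does not fit the design. This part stands: the loss may be very small.
- **Barrack clustering is unquantified.** Participants were randomized individually, and barrack number, size and ICC are all unknown. This stands too.

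A reader might infer that the P value and interval are shown to be wrong, or that segregated housing makes the test anticonservative by a known amount. The article supports neither. Ignoring stage leaves a valid test that errs on the safe side. Clustering would act in the opposite direction by an amount that depends wholly on assumed inputs, so no net error can be derived.

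**Conclusion.** The point holds as a mismatch between design and analysis that is cheap to correct. Stage defines the randomization strata and is described as prognostic, but the named test ignores it and the role of the adjusted model is left open.

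The cost is efficiency, not validity. Over the assumed splits from 25/25% to 10/50%, the SE is 0% to about 10% too large, true alpha lies between about 0.05 and 0.03, and 0 to about 4 points of power are lost. These figures rest on equal stage sizes, a common odds ratio, 706 evaluable per arm and stage-specific rates that the article does not give. The gain from stratifying is near zero if both strata are scored only at stage I altitude.

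Separate housing is a risk to be examined or acknowledged. It is not a demonstrated error in the P value or the power.

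**What to change.** Before the analysis is finalised:

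1. Name one primary comparison of AMS incidence, adjusted for stage: either a Cochran-Mantel-Haenszel test, or logistic regression with arm, stage, prior altitude exposure (first-time or returning) and baseline LLSS, all fixed in advance.
2. Report a standardized risk difference with 95% CI, and the effect within each stage.
3. Keep the chi-square test as supportive.
4. If barrack was recorded and each arm had several, add a sensitivity analysis with barrack-robust standard errors and a small-sample correction. Barracks are nested within arm, so with a single barrack per arm per stage no model can separate barrack from treatment. In that case, or if barrack was not recorded, list segregated housing as a limitation.

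Items 1 to 3 need wording only. Stage is known from randomization, baseline LLSS is in the study schedule (Table 3), and prior exposure is already a named baseline variable. Results reports that analysis is in progress, so the change can still be made. Item 4 depends on housing data that the article does not mention. Its interval could be wider than the primary one: by √1.78 = 1.33 at the top of the assumed range, and by about 1% at the bottom (√1.02).

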### Blinding

The study is open-label; however, to minimize any potential bias, the research staff assigned to assess the study outcomes will be blinded to the allocation of participants to the study groups. In addition, laboratory technicians analyzing blood samples were blinded through the use of coded specimens. The intervention team (Ayurveda practitioner and yoga instructor) had no role in outcome assessments, data entry, or laboratory procedures. The assessment team functioned independently and interacted with participants only at scheduled assessment time points. They were instructed not to inquire about participants’ allocation or intervention experiences. Each participant was assigned a unique study ID; all CRFs, questionnaires, and lab requisitions contained only this ID and not the allocation label. Further, statistical analysis will be conducted by an independent data analysis team not involved in intervention delivery or participant contact.

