## Results

The study was funded in March 2023. The data collection was completed in December 2023. A total of 1660 participants were enrolled in the study. The analysis of the study data is in progress. The study outcomes are expected to be published by December 2026.

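### AMS incidence is to be tested by an unadjusted chi-square and also modelled with an open, data-dependent covariate list, and the plan does not say which result decides

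*Protocol article*

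**What the plan says.** All of this is in the Statistical Methods section of the protocol article unless another place is named.

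- Categorical data are compared between groups by a chi-square test, the only between-group test given for such data. Outcome Measures reports the primary outcome as proportions.
- On covariates: "Baseline variables, such as age, prior altitude exposure, and hydration-related indicators, will be examined descriptively and adjusted in multivariable models where relevant".
- On the primary outcome by name: "Regression analysis will be performed to study the effect of confounding variables on the incidence of AMS".
- On early descent, with no outcome named: "The data of participants having early descent will be analyzed with censored data models".
- One threshold covers everything: a P "value less than .05 will be considered significant".
- Sample Size: "To achieve a statistical power of 90% and a CI of 95%, an initial sample size of 722 per group was calculated", for 25% AMS in the control group against 18% in the Ayush group.
- Results: data collection ended in December 2023, and "The analysis of the study data is in progress".

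No sentence says which analysis of AMS incidence decides the trial.

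**The concern.** The covariate rule is open in two ways. The variables are given as examples, and whether each enters a model is judged after the baseline data have been described. Beside it stands a crude test of the same outcome at the same threshold. A crude and an adjusted estimate of one treatment effect can fall on opposite sides of .05, and the plan does not say which to believe when they do.

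Two things are at stake. The first is the error rate, if the more favourable result were the one reported. The second is precision. Covariates earn their place by predicting the outcome. Selecting them by observed imbalance discards most of what they could contribute, even when nobody is choosing among results.

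**Working it through.** **1. The plan's own figure.** Inputs from Sample Size: p1 = 0.25, p2 = 0.18, 90% power, two-sided 0.05 (sidedness is not stated, but two-sided reproduces the figure). With the mean proportion 0.215:

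n = [1.960 × √(2 × 0.215 × 0.785) + 1.282 × √(0.25 × 0.75 + 0.18 × 0.82)]² / 0.07²

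= [1.960 × 0.5810 + 1.282 × 0.5789]² / 0.0049 = 1.8806² / 0.0049 ≈ 721.8, so 722 per group.

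This is the formula for an unadjusted comparison of two proportions, so the sample size fits the chi-square test. Power at 722 per group is 90.0%. After 15% attrition, 830 × 0.85 ≈ 705 per group remain, and power is 89.3%.

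**2. Error rate under no treatment effect.** The documents do not say how strongly the covariates predict AMS, so a range was assumed.

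*Simulation A.* 705 per arm, about 25% AMS, 3 or 5 independent covariates with odds ratio 1.35 to 1.65 per SD, linear-probability Wald tests, 6,000 trials per scenario (3,000 for the subset search).

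| Rule for claiming success | False-positive rate |
|---|---|
| Crude test only | 5.1–5.3% |
| Fixed covariate set, always included | 5.0–5.4% |
| Adjust only if standardised difference > 0.1 | 4.8–5.1% |
| Crude or fully adjusted | 6.2–7.3% |
| Any subset of 3 covariates | 6.6–7.9% |
| Any subset of 5 covariates | 8.9–11.0% |

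*Simulation B.* 722 per arm, three covariates, logistic regression, 4,000 trials per scenario, each scenario run with 0% and 15% censoring. The last column also admits a log-rank test over 7 days.

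| Log odds ratio per SD | Crude or fully adjusted | Crude, any of 7 covariate subsets, or log-rank |
|---|---|---|
| 0 | 5.3–5.4% | 5.6% |
| 0.3 | 6.3–6.5% | 7.3–7.4% |
| 0.6 | 6.9–7.5% | 8.8–9.4% |
| 0.8 to 1.0 | 6.8–7.3% | 10.2–10.7% |

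Each analysis alone gave 4.0 to 5.5%. The Monte Carlo standard error is √(0.05 × 0.95 / 4000) ≈ 0.34 points. A further run under assumed strengths gave about 6.5 to 8% for crude-or-adjusted. The multiplicity formula for three independent tests, 1 − 0.95³ = 14.3%, does not apply, because these test statistics correlate at about 0.84 to 0.999.

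**3. Power at 25% against 18% (Simulation A).**

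| Analysis | Power |
|---|---|
| Crude | 89.1–89.9% |
| Adjust only for visible imbalance | 89.6–90.3% |
| Fixed covariate set | 90.5–93.4% |

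Setting low end against low end and high against high, the fixed set gains 90.5 − 89.1 = 1.4 to 93.4 − 89.9 = 3.5 points. Imbalance-driven adjustment gains 89.6 − 89.1 = 0.5 and 90.3 − 89.9 = 0.4.

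**4. What was recorded.** Randomization was done separately by altitude stage. Table 3 has baseline rows for demographics and medical history, vital parameters including SpO2, and the Lake Louise score. Study Participants distinguishes first-time from returning sojourners. Hydration-related indicators are not defined and have no row of their own. Blood counts and kidney function tests were taken at screening and might supply one.

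**The case against.** The strongest reply is that the plan already points to one primary test. The outcome is a proportion, chi-square is the only between-group test for categorical data, and the 722 comes from the matching formula. The regression is described as a study of confounders, not as a second test of treatment. A statistical analysis plan that is not shown may name the deciding analysis and the covariates. Most of this stands: chi-square is the likeliest intended primary, and silence on detail in a condensed article would be no finding. What remains is that the article does state a covariate rule, and it is a poor one that a good analysis plan would have to replace.

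Three stronger readings are tempting, and the documents support none of them.

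- *The real false-positive rate is above 5%.* A reader might infer this from the single threshold over several analyses. But no sentence says that success may be claimed on any of them. If chi-square decides, the rate is 5%, and adjusting by observed imbalance does not inflate it either.
- *The censored-data models are a further primary test.* Outcome Measures introduces early descent with the secondary visits up to day 120, and Table 3 has no Lake Louise score at early descent. In Simulation B the log-rank and chi-square statistics correlated at 0.995 to 0.998, so such a model would add almost nothing.
- *The analysts are unmasked.* The Blinding section says only that "statistical analysis will be conducted by an independent data analysis team not involved in intervention delivery or participant contact". It adds that case report forms carry a study ID and no allocation label, while Allocation Concealment has the opened slip attached to the form. That settles nothing either way.

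It can also be said that naming chi-square would be enough. For the error rate that is true, but it forgoes the power gain and ignores the randomisation stratum.

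**Conclusion.** The point holds in a limited form. The plan sets an unadjusted test of AMS incidence beside adjustment by an open, data-dependent rule, and names no deciding result. The error rate is 5% if chi-square decides. It would be about 6 to 8% only if either the crude or an adjusted result could carry the claim and the covariates are prognostic, and up to about 11% if the covariate subset could be picked freely. With covariates that do not predict AMS, the excess almost vanishes. The loss from the rule as written is in power: roughly 1 to 4 points are available from a fixed prognostic set, and most of that is lost when adjustment follows visible imbalance.

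All of these sizes rest on assumed covariate strengths and, in Simulation A, on independent covariates and a linear-probability model. The sample size is not affected.

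**What to change.** Before arm labels are used, name one deciding analysis of AMS incidence: a logistic model reported as a standardised risk difference with 95% CI. Force in altitude stage, as the randomisation stratum, and a fixed set of recorded baseline variables whatever their observed balance: age, first-time versus returning sojourner, baseline Lake Louise score and baseline SpO2. Use hydration-related indicators only if they map to a named variable recorded at screening or baseline. Label the chi-square test and any other regression of AMS incidence as supportive, unable by themselves to carry the claim. If arm labels have already been used in the analysis under way, the report should say so.

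The cost is a few sentences in the analysis plan. No new data are needed and N is unchanged. The downside is that the sponsor gives up the freedom to choose the model after seeing results.
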